### Sample size

We calculated the sample size, i.e. the duration of recruitment, keeping into account the number of emergency calls and the number of emergency room admissions for suspect stroke.

For the ES the mean number of patients per 19 clusters was about 50 (see figure 2). The estimate percentage of correctly transferred patients, based on the Information System of Emergency Rooms in 2003, is 47%. We assumed an intra cluster correlation of ICC = 0.05. Under this assumption we decided 6 months duration, i.e. 25 patients per cluster, to obtain a power of 95% to detect a difference of 50% in rates between the two groups, i.e. reaching about 70% of correctly transferred patients in the treated group, with a = 0.05.

For the emergency rooms the mean number of patients per 14 clusters was about 110. The estimate of correctly transferred patients, based on the Information System of Emergency Rooms in 2003, is 14%. We assumed an intra cluster correlation of ICC = 0.05. Under this assumption and with a duration of 6 months, i.e. 55 patients per cluster, to obtain a power of 95% to detect a difference of 150% in rates between the two groups, i.e. reaching about 35% of correctly transferred patients in the treated group, with a = 0.05.

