**Methods/design:**

Two-arm cluster-randomised trial (C-RCT). 16 emergency services and 14 emergency rooms were randomised either to arm 1 (comprising a training module and administration of the guideline), or to arm 2 (no intervention, current practice). Arm 1 participants (152 physicians, 280 nurses, 50 drivers) attended an interactive two sessions course with continuous medical education CME credits on the contents of the clinical pathway. We estimated that around 750 patients will be met by the services in the 6 months of observation. This duration allows recruiting a sample of patients sufficient to observe a 30% improvement in the proportion of appropriate diagnoses.

Data collection will be performed using current information systems. Process outcomes will be measured at the cluster level six months after the intervention. We will assess the guideline recommendations for emergency and pre-hospital stroke management relative to: 1) promptness of interventions for hyperacute ischaemic stroke; 2) promptness of interventions for hyperacute haemorrhagic stroke 3) appropriate diagnosis. Outcomes will be expressed as proportions of patients with a positive CT for ischaemic stroke and symptoms onset <= 6 hour admitted to the stroke unit.

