#### Primary outcome

- proportion of patients with a positive CT for ischaemic stroke and symptoms onset <= 6 hour admitted to the stroke unit

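### The stated 95% power is for an undefined transfer rate among suspected strokes, and the Abstract names a third target, so no stated power applies to the primary outcome

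*Protocol article*

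**What the plan says.** The protocol article gives three different targets.

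- **Primary outcome section:** "proportion of patients with a positive CT for ischaemic stroke and symptoms onset <= 6 hour admitted to the stroke unit". This limits the population by CT result, stroke type and time since onset.
- **Sample size section:** the duration was set from "the number of emergency calls and the number of emergency room admissions for suspect stroke". For emergency services (ES), "For the ES the mean number of patients per 19 clusters was about 50", and six months gives "25 patients per cluster, to obtain a power of 95% to detect a difference of 50% in rates between the two groups". The starting point is: "The estimate percentage of correctly transferred patients, based on the Information System of Emergency Rooms in 2003, is 47" per cent, and the intervention arm is expected to rise to roughly 70%. For emergency rooms (ER), the section uses 14 clusters, 55 patients per cluster over six months, and a rise from 14% to about 35%, also at 95% power. Both calculations use ICC 0.05 and alpha 0.05. *Correctly transferred* is not defined, and no restriction by CT result or onset time is stated.
- **Abstract, Methods/design:** "This duration allows recruiting a sample of patients sufficient to observe a 30% improvement in the proportion of appropriate diagnoses". No baseline or power level is given.

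The Discussion uses 14% and 47% again, as the proportions of cases directly admitted to the stroke unit. Their bases there are ambulance transports and emergency room admissions.

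**The concern.** A power figure belongs to one endpoint in one population. Here the population sized is suspected stroke and the population analysed is a subset of confirmed stroke. The Discussion suggests that the numerator, stroke-unit admission, is close to that of the primary outcome, so the mismatch lies mainly in the denominator. The protocol recognises the excluded groups: haemorrhages, late arrivals and unconfirmed strokes each appear in its secondary outcomes.

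The Abstract compounds this. An improvement in diagnoses is neither the primary outcome nor the endpoint powered, and 30% matches neither effect in the Sample size section.

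The Sample size section equates sample size with length of recruitment, so an overcounted denominator could mean that six months is too short. The Background says the results will decide on adoption across the region. A null primary result could then be read as a negative finding at 95% power, which the plan has not established.

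**Working it through.** **Inputs.** From the Sample size section: ES 19 clusters, m = 25, 47% v 70%; ER 14 clusters, m = 55, 14% v 35%; ICC 0.05; alpha 0.05. Two-sided testing and 1:1 allocation are my assumptions, as neither is stated there.

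**Formulas.** With k clusters in total:

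- DE = 1 + (m − 1) × 0.05
- effective n per arm = k × m / (2 × DE)
- power = Φ{[|p1 − p2|√n − 1.96√(2p̄(1 − p̄))] / √[p1(1 − p1) + p2(1 − p2)]}, where p̄ is the mean of p1 and p2 (pooled variance under the null).

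**Step 1: reproduce the plan's figure.**

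- ES: DE = 1 + 24 × 0.05 = 2.2; n = 19 × 25 / (2 × 2.2) = 108; power 93.5%.
- ER: DE = 1 + 54 × 0.05 = 3.7; n = 14 × 55 / (2 × 3.7) = 104; power 94.6%.

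Unpooled variance gives 94.1% and 95.3%. The stated 95% is therefore about right, provided all 25 and 55 patients per cluster count towards the endpoint.

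**Step 2: restrict the denominator.** The Background gives 80% of strokes as ischaemic. The share CT-positive with onset within 6 hours is not in the article; I assume a share g from 20% to 60% of the ischaemic cases. Then m = 25 × 0.8 × g for ES and 55 × 0.8 × g for ER. Rates and ICC are held as stated.

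| g | ES m | ES power, 19 clusters | ES power, 16 clusters | ER m | ER power, 14 clusters |
|---|---|---|---|---|---|
| 20% | 4 | 47% | 41% | 8.8 | 64% |
| 40% | 8 | 70% | 63% | 17.6 | 82% |
| 60% | 12 | 81% | 74% | 26.4 | 88% |

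Unpooled variance adds about 1 to 2 points, taking the top row of each range to 83%, 76% and 89%. Removing only the non-ischaemic 20% (m = 20 and 44) leaves 90.9% for ES with 19 clusters and 93.3% for ER.

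The 16-cluster column is shown because the Abstract speaks of 16 emergency services where the Sample size section uses 19 clusters. That is a separate discrepancy: with all 25 patients counted, 16 clusters already give 88.9%.

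**Step 3: compare the Abstract's target.** The Sample size effects are 23 points (70 − 47) and 21 points (35 − 14), stated there as 50% and 150% relative. A 30% improvement is neither. Applied as a relative gain to the transfer baselines with all patients counted, it gives 55% power for ES (47% to 61.1%, 19 clusters) and 13% for ER (14% to 18.2%). Read as 30 points, power exceeds 99% in both. These figures only show that the two sections do not describe the same target, because the Abstract's outcome is diagnosis, not transfer.

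**The case against.** The strongest reply is that the rates may already fit a narrower group. In the illustration the eligible share is 0.8 × 20% to 0.8 × 60%, or 16 to 48% of counted patients. A 47% stroke-unit rate over all suspected strokes would then mean that many ineligible patients were admitted there. So the 2003 rate may rest on a narrower denominator, or *correctly transferred* may be a composite of the right destination for each stroke type and onset time. This stands as a reason not to treat the table as the trial's real power. It does not rescue the 95%: under either reading the endpoint is undefined and is not tied to the primary outcome.

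It is also fair that narrowing the population would change the baseline, whereas the table holds it fixed; power could move either way on that account.

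Three stronger readings are tempting and not supported:

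- *That the sample size arithmetic is wrong.* It reproduces within 2 points.
- *That true power is known to be far below 95%.* The eligible share and the baseline among eligible patients are not in the article. With 80% of counted patients eligible, power stays above 90% at the stated rates.
- *That the Abstract's 30% claim is false.* It gives no baseline or power level and concerns another outcome. It is inconsistent with the Sample size section, which is all that can be said.

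Condensation into an article does not explain the mismatch. The article chose to state an endpoint, effects and a power, and these disagree.

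**Conclusion.** The point holds as a mismatch of endpoint and population. The article's 95% applies to an undefined transfer rate, with numbers drawn from suspected-stroke calls and admissions. The Abstract's 30% applies to a third outcome. Neither is a power statement for stroke-unit admission among CT-positive ischaemic strokes within 6 hours.

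At the stated rates and ICC, every exclusion from the counted patients lowers power. The direction is therefore clear under those conditions, but the amount is not. The illustrative ranges of 47 to 81% (ES, 19 clusters) and 64 to 88% (ER) rest on an assumed share within 6 hours, on applying the 80% ischaemic figure for strokes to suspected strokes, and on unchanged baseline rates.

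The Discussion attaches 14% to ambulance transports and 47% to emergency rooms, the reverse of the Sample size section. That needs its own reconciliation and is not needed for this conclusion: with the rates exchanged, the all-patient power is 95.3% for ES and 92.6% for ER.

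**What to change.** 1. Define *correctly transferred* and state how it maps to the primary outcome, including the denominator of the 2003 rates.
2. From the routine information systems, count per cluster the patients who are CT-positive for ischaemic stroke with onset within 6 hours, and obtain their baseline stroke-unit admission rate.
3. Restate the power, or the detectable difference, for the primary outcome on those figures, and say whether six months still suffices.
4. Replace the Abstract's 30% sentence with the same endpoint, effect and power as the revised Sample size section.

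The cost is a small data query and a rewritten paragraph, and the stated power will probably be less favourable. The Data collection section says the existing systems suffice to measure the outcomes. It does not say that the 2003 records hold CT result and onset time, so that should be checked first. If they do not, the eligible share should be given as an explicit assumption with a range.

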## Methods/design

### Participants

We identified all the emergency services referring to the two stroke units presently available in Rome (figure 1). There were 47 entities comprising 18 emergency rooms and 29 emergency service stations (52 ambulances) from which we created 20 clusters. The criteria for cluster creation was grouping together the services sharing personnel and/or referring patients each other (figure 2-table 1).

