**Figure 2 F2:**
[figure not shown]
**Flow chart of randomization procedure. **Overall we had 20 units of randomization (cluster) of which 10 are couples composed of one ES+1ER on the basis of closeness (usually the ES is situated in the same place of the ER, or systematically refers patients in the same closest ER); 6 are ES and 4 are ER which could not be matched.

**Table 1 T1:** Availability of ambulances and organization of structures in the study area, as reported April 2005.

**Place/Area**	**Emergency Medical Services (ES)**	**Emergency room (ER)**	**Notes**

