**ASL RMA**			
S. Giacomo	full staffed ambulance – ambulances with medical doctors	ER level I	ES and ER randomized independently
Nomentano	Red Cross (as ALS)	-	
Arno-Treviso	3 BLS + 1 full staffed ambulance – ambulances with medical doctors	-	
Addolorata	3 BLS + 1 ALS – ambulances with medical doctors	-	
Marcigliana	1 BLS	-	

Participants are all the workers belonging to the services enclosed in the study (enclosing the ambulances' drivers).

About 152 physicians, 280 nurses, 50 drivers will be trained on the contents of the clinical pathway. We estimated that around 750 patients will be met by the services in the 6 months of observation.

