### Sequence generation and allocation

To avoid contamination due to personnel turnover, the entities were grouped into 20 clusters according to geographical nearness and personnel sharing procedures. Clusters were stratified according to their characteristics:

• Couples of one emergency service and one emergency room (usually working together in the same geographical area) (n°10)

• Groups of emergency services (n°6)

• Only emergency rooms (n°4).

Clusters were attributed sequential numbers and sample function of STATA 7 (StataCorp LP 2005) was used to generate random numbers. We utilized the Italian lottery extracted number of 6th November 2004 in Rome as seeds number for generating the random sequences.

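### The ES power calculation uses 19 clusters, but only 16 randomised clusters contain an ES; with 16 the power is about 89–93%, not the stated 95%

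*Protocol article*

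**What the plan says.** The Sample size section treats the two types of service separately. For the ES it states "For the ES the mean number of patients per 19 clusters was about 50 (see figure 2", then takes 25 patients per cluster over six months, a baseline of 47%, a target of about 70% (a 50% relative increase), ICC 0.05 and alpha 0.05, and claims 95% power. For the ER it uses 14 clusters of 55, 14% v about 35%, with the same ICC, alpha and power.

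The randomised structure appears in three places:
- Sequence generation and allocation lists three strata: "Couples of one emergency service and one emergency room (usually working together in the same geographical area) (n°10"), "Groups of emergency services (n°6") and "Only emergency rooms (n°4").
- The legend of figure 2 repeats it: 10 couples, and of the remaining units "6 are ES and 4 are ER which could not be matched".
- The abstract says "16 emergency services and 14 emergency rooms were randomised".

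On patient volume, the abstract and the Participants section both give one figure: "We estimated that around 750 patients will be met by the services in the 6 months of observation".

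**The concern.** The strata give 10 + 6 = 16 clusters with an ES and 10 + 4 = 14 with an ER. The ER paragraph uses 14; the ES paragraph uses 19 and cites figure 2, whose legend gives 16. No combination of 10 couples, 6 ES groups and 4 ERs yields 19 clusters containing an ES. In a cluster trial the number of clusters drives power, so the published figure describes a design larger than the one randomised. What is at stake is the size of the ES type II error: stated as 5%, it may be about twice that.

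A second matter is the patient total. The section sets the recruitment period from patient volume, yet it does not show how 750 relates to 25 per ES cluster and 55 per ER cluster.

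**Working it through.** **Inputs** (Sample size section): ES p1 = 0.47, p2 = 0.70 (or 0.705, which is exactly 1.5 × 0.47), m = 25; ER p1 = 0.14, p2 = 0.35, m = 55; ICC = 0.05; alpha = 0.05. Assumed because not stated: two-sided alpha, 1:1 allocation by cluster, equal cluster sizes.

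**Formulas.** Design effect DE = 1 + (m − 1) × ICC. Effective patients per arm n = (K/2) × m / DE, with K the number of clusters. Standard error SE = √{[p1(1 − p1) + p2(1 − p2)]/n}. Power (unpooled) = Φ[(p2 − p1)/SE − 1.96]. The pooled version uses the pooled SE under the null in the critical value.

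**Reproducing the plan's ES figure, K = 19.** DE = 1 + 24 × 0.05 = 2.20; n = 9.5 × 25/2.20 = 108.0; SE = √(0.4591/108.0) = 0.0652. Power = Φ(0.23/0.0652 − 1.96) = Φ(1.57) = 94.1% unpooled, 93.5% pooled. With p2 = 0.705 it is 95.1% unpooled, 94.4% pooled. The stated 95% reproduces.

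**Reproducing the ER figure, K = 14.** DE = 1 + 54 × 0.05 = 3.70; n = 7 × 55/3.70 = 104.1. Power 94.6% pooled, 95.3% unpooled. The stated 95% reproduces.

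**Sidedness.** A one-sided alpha would give 96.7% (ES, 19 clusters) and 97.4% (ER), both pooled. Two-sided alpha fits both stated figures better.

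**ES with the randomised number of clusters, K = 16.** At 25 each, n = 8 × 25/2.20 = 90.9. Keeping the total of 19 × 25 = 475 patients gives 475/16 = 29.7 each, DE = 2.43, n = 97.6.

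| ES clusters × patients | Total | Power at 70% (pooled, unpooled) | Power at 70.5% (pooled, unpooled) |
|---|---|---|---|
| 19 × 25 | 475 | 93.5%, 94.1% | 94.4%, 95.1% |
| 16 × 25 | 400 | 88.9%, 89.9% | 90.3%, 91.2% |
| 16 × 29.7 | 475 | 90.9%, 91.8% | 92.2%, 93.0% |

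**Baseline rates.** The Discussion assigns 14% to ambulance transports and 47% to ER admissions, the reverse of the Sample size section. With 14% v 35% for the ES, 16 × 25 gives 91.5% pooled (92.4% unpooled). With 47% v 70% for the ER, 14 × 55 gives 92.6% pooled.

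**Small-sample variant, for information.** A cluster-level t-test on K − 2 degrees of freedom would give ES power of 85.3–86.9% (16 × 25) or 87.6–89.1% (16 × 29.7), and ER power of 91.5%.

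**The total of 750.** 16 × 25 + 14 × 55 = 400 + 770 = 1170. Three readings of 750 (pooled power):
- ER total with ambulance patients included in it: 770 is within 3% of 750. At 750/14 = 53.6 per ER cluster, ER power is 94.5%, so nothing is lost.
- 30 services × 25 = 750: the ER would have 25 per cluster and 87.6% power.
- Non-overlapping total shared in proportion (750/1170 = 0.641): ES 16 × 16.0 gives 81.3%; ER 14 × 35.3 gives 91.5%.

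**The case against.** The strongest reply is that the loss is small. The figure given is a mean over 19 units, and regrouping the same services into 16 clusters does not remove patients. On that view each cluster has 29.7 patients, and power drops by only about 2 to 3 points on any one method. This stands, and it is why the answer is a range rather than a flat 90%. It does not rescue 95%.

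A one-sided alpha would bring 16 × 25 to 93.9% (pooled), close to the claim. It also pushes the ER figure to 97.4%, so it fits the text less well.

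A reader might infer more than the documents support in three respects:
- **That 750 contradicts the calculation.** Adding ES and ER counts to 1170 treats them as different people. The Background says basic ambulances must deliver to the nearest emergency hospital, so the same patient can appear in both counts, and the ER total alone is close to 750. The Sample size section fixes the six months from 25 and 55 per cluster and does not use 750. What remains is that its derivation is not shown.
- **That the ER power is also wrong.** It reproduces with 14 clusters. The lower t-test figures rest on a test that the document does not name.
- **That the mismatch in entity counts undermines the power.** Participants states "There were 47 entities comprising 18 emergency rooms and 29 emergency service stations", against 16 and 14 in the abstract. Grouping of ES stations, and the network changes reported in the Discussion, account for part of this, and these counts do not enter the power calculation.

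**Conclusion.** The ES power is computed for a number of clusters that the randomised design does not have. Under the normal approximation that reproduces the plan's own figures, with two-sided alpha, 1:1 allocation and equal cluster sizes, 16 clusters give about 89–91% at 25 patients each, or about 91–93% with the same 475 patients. The type II error is therefore about 7–11% instead of 5%. The conclusion does not depend on which baseline rate belongs to the ES: with the rates swapped, 16 × 25 gives about 92%, still below 95%.

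The source of 750 is unexplained, but a shortfall is not established. It would cost power only if 750 is a count of distinct patients shared between the two calculations, or 25 per service. The figure 2 drawing was not available, only its legend, which agrees with the strata and the abstract.

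**What to change.** In the Sample size section:
- Replace 19 by 16 ES clusters and state the patients per cluster that follow (25, or 29.7 if the total of 475 is kept).
- Restate ES power as about 90% (25 per cluster) or about 92% (same total), and say that alpha is two-sided if so.
- Leave the ER power at 95% for this method. Optionally note that a cluster-level t-test would give less (about 85–89% ES, about 91% ER).
- First reconcile the baseline rates with the Discussion, so that the restated figures rest on agreed inputs.

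Where 750 appears, say how it was derived and whether patients brought by ambulance are counted again at the ER. If it is a non-overlapping total, restate both powers for it.

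The cost is wording and recalculation only. Neither the randomisation nor the recruitment period needs to change.

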#### Secondary outcomes

- proportion of patients with a positive CT for hemorrhagic stroke and symptoms onset <= 6 hour admitted to a neurosurgical ward

- proportion of patients with a positive CT for hemorrhagic or ischaemic stroke or symptoms onset >6 hour admitted to the nearest hospital

- proportion of ICD9CM code for stroke in emergency setting confirmed in the hospital discharge data

- proportion of patients with stroke confirmed by CT results

- proportion of patients with ischaemic stroke receiving treatment within 6 hour of symptoms onset

All the outcomes will be reported at cluster level and will be cross-checked by the integration of data from the available information systems.

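### The two stated 95% powers ignore the small number of clusters, and the ES figure counts 19 clusters where the rest of the article shows 16

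*Protocol article*

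**What the plan says.** The Sample size section makes two separate calculations, both with ICC 0.05 and alpha 0.05. It does not say whether alpha is one- or two-sided.

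- **ES:** "For the ES the mean number of patients per 19 clusters was about 50 (see figure 2". Half a year of that gives "6 months duration, i.e. 25 patients per cluster, to obtain a power of 95% to detect a difference of 50% in rates", from 47% to about 70%.
- **ER:** "For the emergency rooms the mean number of patients per 14 clusters was about 110". Six months gives 55 per cluster, "to obtain a power of 95% to detect a difference of 150% in rates between the two groups", from 14% to about 35%.

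Only mean cluster sizes appear. No spread of sizes and no small-sample allowance is mentioned. The Outcomes section adds: "All the outcomes will be reported at cluster level".

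The cluster make-up is described elsewhere. Participants: "There were 47 entities comprising 18 emergency rooms and 29 emergency service stations". Figure 2 legend: "10 are couples composed of one ES+1ER on the basis of closeness", with six further ES units and four further ER units, 20 in all. Sequence generation and allocation gives the same split, including "Groups of emergency services (n°6" in number. The Abstract says that 16 emergency services and 14 emergency rooms were randomised.

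**The concern.** Two things do not fit.

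First, with 14 ER clusters a comparison of cluster-level results has 12 degrees of freedom. A power calculation with a normal critical value treats the between-cluster variance as known and overstates power at that size.

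Second, the ES calculation counts 19 clusters, but 10 couples plus 6 ES groups make 16 units with an ES. The ER count agrees throughout: 10 + 4 = 14.

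The results are meant to decide whether the pathway is adopted across the region (Background). A null result would be read as coming from a trial with a 5% type II error when the design's own inputs imply a larger one.

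**Working it through.** **Inputs (Sample size section).** ER: 14 clusters, m = 55, 14% v 35%. ES: 19 clusters, m = 25, 47% v 70%. ICC 0.05, alpha 0.05. The allocation ratio is not stated, so I assume near-equal arms: 7 v 7 ER, 9 v 10 ES on 19, 8 v 8 ES on 16.

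**Formulas.**
- Design effect: DE = 1 + (m − 1) × ICC.
- Unpooled standard error: SE = √{(DE/m) × [p₁(1 − p₁)/k₁ + p₂(1 − p₂)/k₂]}, with k clusters per arm. The pooled form uses the average proportion in both arms.
- λ = |p₁ − p₂| / SE.
- Normal power: Φ(λ − 1.960).
- t power: noncentral t with noncentrality λ, on clusters − 2 degrees of freedom.

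**Step 1: reproduce the stated 95%.**
- ER: DE = 1 + 54 × 0.05 = 3.7. SE = √{(3.7/55) × (0.1204 + 0.2275)/7} = 0.0578. λ = 0.21/0.0578 = 3.63. Normal power is 95.3% (pooled 94.1%).
- ES, 19 clusters: DE = 1 + 24 × 0.05 = 2.2. SE = √{(2.2/25) × (0.2491/9 + 0.2100/10)} = 0.0655. λ = 0.23/0.0655 = 3.51. Normal power is 94.0% (pooled 93.0%).

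The stated figures therefore reproduce to within about two points.

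**Steps 2 and 3: t test, then the ES count.** The range in each cell is pooled to unpooled, at equal cluster sizes.

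| Case | DE | df | Two-sided normal | Two-sided t | One-sided 5% t |
|---|---|---|---|---|---|
| ER, 14 clusters, m = 55 | 3.70 | 12 | 94.1 to 95.3% | 89.8 to 91.5% | 95.2 to 96.2% |
| ES, 19 clusters, m = 25 | 2.20 | 17 | 93.0 to 94.0% | 89.9 to 91.2% | 95.0 to 95.8% |
| ES, 16 units, m = 25 | 2.20 | 14 | 88.2 to 89.9% | 83.3 to 85.3% | 91.1 to 92.4% |
| ES, 16 units, m = 475/16 = 29.7 | 2.43 | 14 | 90.3 to 91.8% | 85.8 to 87.6% | 92.7 to 93.8% |

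The last row keeps the patient total of 19 × 25 = 475 and spreads it over 16 units. On 16 units even the normal test falls short of 95%.

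A beta-binomial simulation of a two-sided cluster-level t test (40,000 runs, equal sizes) agrees: ER 91.2%, ES 90.3% on 19 clusters, ES 84.3% on 16 units at m = 25.

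**Step 4: unequal sizes, as an illustration only.** Each couple holds one ES station, so 29 − 10 = 19 stations fall in 6 groups, about 3.17 each. If every station had the same patient volume, sizes would be 10 × 1 and 6 × 3.17, with mean 29/16 = 1.81, SD 1.05 and CV 0.58. Then:
- DE = 1 + ((1 + CV²) × m − 1) × ICC = 1 + (1.336 × 25 − 1) × 0.05 = 2.62.
- ES power on 16 units is 76.5 to 78.7% at m = 25, and 78.9 to 81.0% at m = 29.7.

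The equal-volume premise is not in the article.

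**The case against.** **Sidedness and test are not stated.** This stands in part. A one-sided 5% t test gives about 95% for ER and for ES on 19 clusters, so the normal test is the only route to 95% only under two-sided alpha. It does not rescue ES on 16 units (91 to 94%). Reporting outcomes by cluster names no test, and the test may properly be left to an analysis plan. The power claim, however, is fixed in this article.

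**Inputs are approximate.** True: with ICC 0.04 the ER t-test power returns to 94.9% (unpooled). But the article chose 0.05 and claims 95% at that value.

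**A reader might infer that ES power is about 80%, as a consequence of the normal test and the mean cluster size.** The documents do not support that. With the stated 19 clusters the t test gives 90 to 91%. Reaching about 80% needs three things together: 16 units, the t test and a CV near 0.58. That CV treats station counts as patient volumes. Table 1 shows stations of very different capacity (some open 12 hours, one for inter-hospital transfer only, some with several ambulances), so grouping small stations could even out the volumes.

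**A reader might also derive a CV of 0.35 for ERs** by placing two ERs in each of the four ER-only clusters. The Figure 2 legend describes four ERs that could not be matched, and Table 1 marks four places, each with one ER, as having ES and ER randomised independently. That layout is therefore unsupported, and I give no ER figure for unequal sizes.

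**Conclusion.** The point holds in this form. At two-sided 0.05, ICC 0.05 and equal cluster sizes, the stated 95% becomes about 90 to 91% for 14 ER clusters and about 90 to 91% for 19 ES clusters. On the 16 ES units shown in three other places it becomes about 83 to 88%, depending on whether 25 per cluster or the total of 475 is held. Type II error is then roughly 9 to 10% for ER and 12 to 17% for ES on 16 units, against the stated 5%.

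Unequal sizes can only lower these values in this calculation. The ES range of about 77 to 81% is conditional on equal volume per station and is not a finding about the design.

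The figures assume near-equal arms and the baselines as given in the Sample size section. The Discussion gives 14% and 47% the other way round, which needs separate reconciliation.

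The consequence is moderate: a stated property of the design is too favourable, but the trial is not made invalid.

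**What to change.** 1. Reconcile the number of ES clusters (16 or 19), and say whether 25 per cluster or the patient total is the fixed quantity.
2. State whether alpha is one- or two-sided.
3. Recompute both powers with a t critical value on clusters minus 2 and DE = 1 + ((1 + CV²) × m − 1) × ICC. Take the CV from the actual 2003 volumes per cluster: the agency running the study maintains the emergency-room system and has access to the 118 system.
4. Restate the powers. Until those volumes are used, the supportable figures at two-sided 0.05 and equal sizes are about 90 to 91% for ER and about 83 to 88% for ES on 16 units, with a note that unequal sizes reduce them. An ES figure of 80% should not be printed unless the actual volumes give it.

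The cost is a recalculation from data in hand and less favourable stated figures. No extra patients or clusters are required.
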